#### Inclusion criteria

(1) Participants must meet the diagnostic criteria for TD as according to the American Diagnostic and Statistical Manual of Mental Disorders, 5th edition (DSM-5); (2) Age between 3 and 14 years old; (3) Have stopped using other drugs for mental illness for more than 3 months before starting the treatment; (4) Self-volunteer as the subject, signed by the child’s guardian, and children aged 8 and above get their own informed consent.

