Energy metabolism may play an important breakthrough in patients with TD. Studies have found that there are differences in neurotransmitters in urine between children with TD and healthy children. Animal models of TD were presented with neurotransmitter abnormalities in cerebrospinal fluid (CSF), detection of neurotransmitters in urine, response to drug therapy that blocks or stimulates neurotransmitters, autopsy findings and neuroimaging studies, which mainly involving dopaminergic, glutamatergic and 5- hydroxytryptamine neurotransmitters [7, 8]. The brain-gut axis is closely related to the occurrence of neuropsychiatric diseases [9]. TD is a chronic neurological disorder. After various clinical observation and animal experiments, the changes of intestinal microflora in patients with TD seem to be specific [10]. The methods of utilizing probiotics and fecal microbiota transplantation in the treatment of TD have shown promising outcomes [11]. The relationship between intestinal microflora and TD as well as the improvement of TD by improving intestinal microflora is rather a new topic, and larger-scale clinical trials are needed to further confirm the influence of intestinal microflora in TD. Therefore, metabonomics detection of urine and feces is beneficial to further study the pathogenesis of TD.

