### Case criteria

This study commenced in September 2023 and is anticipated to be completed by December 2025. Sixty children diagnosed with tic disorder from the Affiliated Hospital of Nanjing University of Traditional Chinese Medicine will be randomly assigned to either the treatment group or the control group, with 30 children in each group. Additionally, 30 healthy children will be recruited for comparison purposes.

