#### Exclusion criteria

(1) TD caused by chorea, hand and foot thrombosis, hepatolenticular degeneration, encephalitis and drug-induced; (2) Patients with mental illness; (3) People with mental retardation; (4) Patients with cardiovascular, liver, kidney and hematopoietic diseases.

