### Testing requirements

The environment of the infrared thermography examination room is relatively stable, the temperature is maintained at 24 degrees Celsius, the relative humidity is less than 70%, the indoor air flows naturally, there is no wind and dust, and there is no direct heat source. Subjects should avoid drinking alcohol, coffee and other irritating foods 24 h before shooting, prohibit from eating too cold or overheated food 1 h before the shooting, avoid strong cold or overheated environment (such as direct blowing under air conditioning), and stop physical therapy and taking drugs 10 min before shooting and avoid leaning on object.

After entering the examination room, the subject should take off his/her shirt and expose the bare shooting area, remove necklaces and other accessories, and hair should not cover the forehead and neck, the subject is required to sit quietly and rest for 15 min to adapt to the ambient temperature, and avoid pressing or scratching the examination area during the rest period.

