##### Fecal sample

To begin, prepare the feces container, wash your hands thoroughly, and wear gloves. Use sterile spoons, provided with the sampling tube cover, to collect 2–3 spoons of fecal samples for each tube. Once collected, immediately place the samples in low-temperature conditions such as liquid nitrogen, dry ice, ice bags, or a refrigerator set at 4 degrees Celsius. Subsequently, promptly transfer the samples to a -80-degree refrigerator for long-term storage.

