#### Multivariate Statistical Analysis

Preprocessed data will be subjected to unsupervised data analysis using Principal Component Analysis (PCA). A score plot will be used to observe clustering of data from different groups and to remove outlier samples. A loading plot will be utilized to identify components that contribute to inter-group variability, with special attention given to excluding prototype compounds and their metabolites. Additionally, univariate analysis such as fold change (FC) and t-tests will be performed to identify components that exhibit significant statistical differences. Pattern recognition methods, such as Partial Least Squares Discriminant Analysis (PLS-DA) and Orthogonal Partial Least Squares Discriminant Analysis (OPLS-DA), will be employed, and targeted programming and execution using languages such as R or C will be based on the characteristics of the analysis data. Integration of HILIC-TOFMS and RPLC-TOFMS data will be conducted to identify differential components. Multiple methods, including t-tests (*p* < 0.05), FC analysis (FC > 2), and PLS-DA (VIP > 1.5), will be used to screen and confirm potential biomarkers that contribute to inter-group differences, thus identifying potential biomarkers associated with acupuncture treatment in children with TD.

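### The plan neither restricts nor records recent probiotic, microbiota-product or antibiotic use before urine and stool sampling, so unbalanced exposure can confound the metabolomics screen, above all TD versus healthy

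*Protocol article*

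**What the plan says.** All references are to the protocol article.

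- **Inclusion criteria.** The items on age and drugs begin "2) Age between 3 and 14 years old; (3) Have stopped using other drugs for mental illness". The only drug restriction, in full, is "Have stopped using other drugs for mental illness for more than 3 months before starting the treatment". Item 1 of the same list requires tic disorder (TD), so the list does not govern the healthy children.
- **Exclusion criteria.** Four items cover secondary causes of tics, mental illness, mental retardation and organ disease, ending with "4) Patients with cardiovascular, liver, kidney and hematopoietic diseases". None concerns products that act on gut flora.
- **Healthy children.** Case criteria says "Additionally, 30 healthy children will be recruited for comparison purposes" and gives no conditions for them.
- **Sampling.** The urine and fecal steps are detailed, for example "Use sterile spoons, provided with the sampling tube cover, to collect 2–3 spoons of fecal samples for each tube", but ask nothing about recent exposure. Thermography does have preparation rules, including "stop physical therapy and taking drugs 10 min before shooting".
- **Rationale.** The Introduction ties gut flora to TD, states "The methods of utilizing probiotics and fecal microbiota transplantation in the treatment of TD have shown promising outcomes", and gives this as a reason for urine and fecal metabolomics.
- **Screen.** Multivariate Statistical Analysis selects candidates by several methods, "including t-tests (*p* < 0.05), FC analysis (FC > 2), and PLS-DA (VIP > 1.5". Outlier samples are first removed on a PCA score plot with no stated cut-off. No adjustment for exposure is described.

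**The concern.** On the article's own account, a probiotic is both a possible treatment for the condition and something that acts on the system being measured. The plan washes out psychiatric drugs but leaves this exposure free and unrecorded. If more children in one group are exposed, a metabolite changed by the product can be reported as a marker of TD or of acupuncture. Without a record, nobody can tell afterwards.

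Three contrasts are open to this, to different degrees. TD versus healthy is not randomised, so nothing balances exposure. Baseline versus week 12 is open to products started or stopped during the 12 weeks. Treatment versus control is balanced in expectation, so only chance imbalance or exposure after allocation matters.

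**Working it through.** The plan gives no figure on exposure. From the documents I take 30 children per group, 60 TD children if the arms are pooled, p < 0.05 and FC > 2. Exposure counts, fold rises and background spread are assumptions. The 30 per group is taken as fixed: 95% versus 55%, two-sided 0.05, gives 23 per arm at 90% power (power is not stated), and 23/0.8 rounds up to 29, close to the stated 30.

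**Step 1: fold change.** If m of n children have a metabolite raised k-fold and nothing else differs, the group mean is multiplied by 1 + (m/n)(k − 1). With n = 30 and k = 10:

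- m = 4: 1 + (4/30)(9) = 2.2
- m = 6: 1 + (6/30)(9) = 2.8

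FC > 2 needs k > 1 + n/m: above 11-fold for 3 exposed, 8.5-fold for 4, 7-fold for 5.

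**Step 2: the t-test ceiling.** However large the rise, t with m exposed of 30 against none of 30 tends to √[m(n − 1)/(n − m)]:

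- m = 3: √(87/27) = 1.80, p = 0.078
- m = 4: √(116/26) = 2.11, p = 0.039
- m = 5: √(145/25) = 2.41, p = 0.019

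So three exposed children seldom suffice in 30 against 30, and four is about the minimum.

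**Step 3: simulation.** Log-normal background, log-SD 0.3, 10-fold rise, equal-variance t-test. The last column is the share of runs with both p < 0.05 and FC > 2.

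| Exposed | Expected FC | Passing |
|---|---|---|
| 4/30 vs 0/30 | 2.2 | 46% |
| 5/30 vs 0/30 | 2.5 | 96% |
| 6/30 vs 0/30 | 2.8 | over 99% |
| 4/30 vs 1/30 | 2.2/1.3 = 1.69 | 0.2% |
| 5/30 vs 1/30 | 2.5/1.3 = 1.92 | 9% |
| 6/30 vs 2/30 | 2.8/1.6 = 1.75 | 2% |
| 3/30 healthy vs 0/60 TD | 1.9 | 29% |
| 4/30 healthy vs 0/60 TD | 2.2 | 80% |
| 6/60 TD vs 0/30 healthy | 1.9 | 1.6% |

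Six against one is the exception among the mixed cases: expected FC is 2.8/1.3 = 2.15, and about 44% of runs pass.

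**Step 4: sensitivity.**

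- 5-fold rise: under 1% with 4 exposed, 13% with 6 (none in the other group).
- 10-fold, log-SD 0.5: 26%, 61% and 88% with 4, 5 and 6. At log-SD 1.0: 11% to 29% across 4 to 6.
- No exposure: about 0% at log-SD 0.5, about 1.5% at log-SD 1.0.
- Falls of 10- to 100-fold in six or fewer children: 0.1% or less at log-SD 0.5 and at most 5% at log-SD 1.0, using raw means. On geometric means with a log-scale t-test, a 100-fold fall in 5 children passes in 69% (log-SD 0.5).

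**Step 5: form of the t-test in the pooled comparison.** Statistical analysis prescribes the Satterthwaite correction for unequal variances; the metabolomics section says only t-tests. With equal variances, the ceiling for 3 of 30 healthy against 60 TD is 0.1/√[(30 × 0.09/88)(1/30 + 1/60)] = 2.55. With the correction it is 1.80, as in Step 2. For 6 of 60 TD against 30 healthy, the two are 0.1/√[(60 × 0.09/88)(1/30 + 1/60)] = 1.81 and √[6(59)/54] = 2.56. Under the correction, then, three exposed healthy children no longer suffice and four can, while six exposed TD children come into range. The 30 against 30 results change little.

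**Step 6: chance imbalance between randomised arms.** At assumed exposure rates of 5% to 20%, a difference of 4 or more arises in 4% to 26% of trials. The damaging pattern, 4 or more against none, arises in 0.2% to 3%.

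**The case against.** The strongest reply is that this is an omission in a condensed article and that a full protocol may hold the missing rule. That has some force, but the numbered eligibility lists are printed and the sampling steps go down to centrifuge speed. A trial run as printed would admit exposed children.

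A reader might also infer that a few exposed children will create a biomarker by themselves. The documents do not support that. It requires nearly one-sided exposure and large rises, and one or two exposed children in the other group mostly remove the effect. The VIP > 1.5 threshold was not simulated, so passing every threshold is not shown. The text also has partial safeguards: PCA outlier removal, the exclusion of prototype compounds and their metabolites, the 80% rule for missing values, and correlation with scale scores. None is aimed at flora-driven changes in endogenous metabolites.

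Three further readings go too far.

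- The inclusion criteria do not admit exposed healthy children. They do not apply to healthy children, for whom nothing is printed.
- The article never mentions antibiotics. That they alter gut flora is general knowledge; only the probiotic argument rests on the text.
- Bias in the YGTSS comparison is not established. Randomisation balances probiotic use in expectation, and children and assessors are to be blinded.

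**Conclusion.** The point holds as a gap in control and recording of exposure. Probiotic, microbiota-product and antibiotic use can confound an unadjusted metabolomics screen whose rationale is partly gut flora. The non-randomised TD-versus-healthy comparison is the most exposed.

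The size is conditional. In 30 against 30, about 4 to 6 exposed children nearly all on one side, with rises near 10-fold, are needed. Against 60 pooled TD children, about 3 to 4 exposed healthy children can suffice, three only with an equal-variance t-test. Exposure rates, fold sizes and background spread are all assumptions. The outcome is secondary and the screen is exploratory, so this is a worthwhile improvement and does not threaten the primary comparison.

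**What to change.** 1. Add one sample-eligibility rule, identical for TD and healthy children: no probiotic, microbiota product or antibiotic within a window before the baseline urine and stool samples, its length fixed in advance with the metabolomics laboratory. If a child was exposed, delay the baseline sample. The rule concerns sampling only and does not ask anyone to stop a product.
2. Ask the same question at week 12. Keep that sample on schedule, because the article fixes the week-12 time point, and flag it if the child was exposed.
3. Repeat the biomarker screen without flagged samples and report both results.
4. Keep all randomised children in the YGTSS comparison and report probiotic use by arm.

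The cost is one rule, one question at two existing visits and one extra run of the screen. A few baseline samples will be delayed, and the repeat screen will have slightly fewer samples. Recruitment is under way, so the change is best made soon, since exposure history is hard to recover later.

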#### Exclusion criteria

(1) TD caused by chorea, hand and foot thrombosis, hepatolenticular degeneration, encephalitis and drug-induced; (2) Patients with mental illness; (3) People with mental retardation; (4) Patients with cardiovascular, liver, kidney and hematopoietic diseases.

#### Drop-out criteria

(1) Those who experience severe adverse reactions after acupuncture. (2) Co-authors who drop out mid-way. (3) Previously received a sufficient course of acupuncture technique rehabilitation intervention.

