**Methods:**

This randomized controlled trial will recruit a total of 90 children, in which they will be divided into non-intervention group and intervention group. The non-intervention group consists of 30 healthy children while the intervention group consists of 60 children with tic disorder. The intervention group will be randomly allocated into either the treatment group or the control group, with 30 children randomly assigned in each group. Children either received acupuncture treatment and behavioral therapy (treatment group) or sham acupuncture treatment and behavioral therapy (control group), 3 treatment sessions per week for a period of 12 weeks, with a total of 36 treatment sessions. Outcome measures include YGTSS, urinary and fecal metabolomics, infrared thermography of body surface including governor vessel. For the intervention group, these outcome measures will be collected at the baseline and 90th day prior to intervention. Whereas for the non-intervention group, outcome measures (excluding YGTSS) will be collected at the baseline.

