## Outcome evaluations

### Primary outcomes

Yale Comprehensive Tic Severity Scale (YGTSS) is the most commonly used scale to evaluate the severity of tic condition in clinic. The scale scores motor tic and vocal tic respectively, and clinicians score them by asking questions from the guardians and observing their performance in clinic. The total score of YGTSS in patients with TD, if it is less than a score of 25, it is considered as mild, a score of 25 to 50 is considered as moderate, and a score of 50 above is considered as severe.

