## Quality control

The YGTSS scale will be assessed by a qualified physician. Standard operating procedures and quality control procedures will be established for observing indicators using infrared thermal imaging, with computer-generated results and traceable data and images. We will analyze and process the data through professional instruments to ensure the accuracy of the data. Prior to the project commencement, researchers received training on the experimental protocol, and the consistency of quantitative symptom and sign assessment standards was tested. Researchers signed a statement of commitment. Researchers should diligently obtain informed consent to ensure that participants fully understand the experimental requirements and are willing to cooperate. Treatment compliance of patients in the experimental group is monitored using the treatment count method. Compliance is calculated as the actual number of treatments received divided by the initially scheduled number of treatments, multiplied by 100%. Compliance rates below 80% or above 120% are considered major violations of the experimental protocol. The results before and after treatment should be communicated to the families of the patients.

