## Data management and monitoring

The researchers will use research medical records to collect data and establish a database. The recorded data in the research medical records will be summarized and analyzed to generate the final conclusions and research report. Upon completion of the study, the database will be locked for security purposes. The personal information of the participants will be treated as confidential. Documents related to quality control, such as original records of data consistency check, numerical range and logic check, and blind audit, will be preserved. Meanwhile, we have trained researchers to establish a good communication relationship with patients. For patients who discontinue or deviate from intervention protocols, we will try to get as much trial data as possible by telephone, if the patient is willing to provide it. In addition, a safety monitoring committee will be established to review and interpret the data of trial. They will review the progress of the trial, independently of the investigators, and decide whether the trial needs to be terminated early solely on the basis of adverse events.

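### Prior acupuncture is a reason to drop a child after randomisation but not to exclude one before it, and session compliance is counted in the real-acupuncture arm only

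*Protocol article*

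**What the plan says.** The Drop-out criteria section of the protocol article has three items. The first is "Those who experience severe adverse reactions after acupuncture" and the third is "Previously received a sufficient course of acupuncture technique rehabilitation intervention". The Inclusion criteria have four items (DSM-5 diagnosis, age, washout of other drugs, consent), and none mentions earlier acupuncture. The Exclusion criteria also have four, ending with "Patients with cardiovascular, liver, kidney and hematopoietic diseases", and they do not mention it either.

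On adherence, the Quality control section says "Treatment compliance of patients in the experimental group is monitored using the treatment count method" and then "Compliance rates below 80% or above 120% are considered major violations of the experimental protocol". The schedule is three sessions a week for 12 weeks, "with a total of 36 treatment sessions". The control-group section gives sham the same duration and period.

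For children who stop or deviate, Data management and monitoring says "we will try to get as much trial data as possible by telephone, if the patient is willing to provide it". The primary outcome, YGTSS, is obtained in person: "clinicians score them by asking questions from the guardians and observing their performance in clinic". Under Randomization, the acupuncturist knows the allocation; subjects, evaluators and analysts do not.

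**The concern.** A trait that is fixed before enrolment belongs in screening. Placed among the drop-out criteria, it lets a child pass eligibility, take a randomisation slot and then be withdrawn. Such children are likely to present, because recruitment is from an acupuncture and rehabilitation outpatient department, alongside posters and WeChat. The article does not say when the item is checked or by whom, and one person in regular contact with the child is unblinded. If the item is applied late and by someone who knows the arm, discretion can enter over who stays.

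The compliance rule has a different fault: it exists for one arm. If sham sessions are not counted, poor attendance cannot be compared between arms, and a per-protocol set with the same limits on both sides cannot be built afterwards.

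What is at stake for the YGTSS result is conditional. If either rule, or drop-out for severe reactions, determines who is analysed or who is scored at week 12, the groups compared are no longer those that were randomised.

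**Working it through.** **1. The eligibility path.** Inclusion (four items) and exclusion (four items) are both silent on prior acupuncture, and drop-out item 3 names it. A child with such a history therefore passes screening at Week -1, is allocated at Week 0 (Table 1) and then meets a drop-out criterion on a fact that was true throughout. The sections conflict on whether this child belongs in the trial.

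**2. The compliance limits.** Scheduled sessions: 3 × 12 = 36, as stated. Lower limit: 0.80 × 36 = 28.8, so 28 or fewer is a major violation. Upper limit: 1.20 × 36 = 43.2, so 44 or more is. A sham child with 28 sessions has no corresponding label.

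**3. The plan's sample size and its loss allowance.** Inputs from Sample size: 95% against 55%, 20% dropout, 30 per group. Power is not stated; 90% is assumed here, with two-sided 5% taken from the Statistical analysis section. With p̄ = 0.75,

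n = [1.96·√(2 × 0.75 × 0.25) + 1.2816·√(0.95 × 0.05 + 0.55 × 0.45)]² / 0.40² = (1.200 + 0.696)² / 0.16 = 22.5, so 23 per arm; 23 / 0.8 = 28.75, so 29.

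This is within one of the stated 30. The allowance is 0.20 × 30 = 6 children per arm. Power on these rates is 96.6% with 30 per arm and 91.9% with 24. Each child dropped for a history known at screening uses up part of that allowance.

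**4. How large a bias could be, if removal decided the analysis.** The documents give no removal shares and no link between removal and outcome, so everything here is assumed: no true effect, 30 per arm, children removed from one arm only.

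Upper bound: with the worst fraction d of a standard normal outcome removed, the mean shifts by φ(z₁₋d)/(1 − d).
- d = 0.10: 0.1755 / 0.90 = 0.195 SD
- d = 0.20: 0.2800 / 0.80 = 0.350 SD

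Removal on a trait correlated ρ with outcome, two-sided t test at 5%, 100,000 simulated trials:

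| Removed from one arm | ρ = 0 | ρ = 0.3 | ρ = 0.5 | ρ = 1 (worst outcomes) |
|---|---|---|---|---|
| 3 of 30: shift | 0 SD | 0.06 SD | 0.09 SD | 0.19 SD |
| 3 of 30: false-positive rate | 5% | 5.5% | 6.7% | 13% |
| 6 of 30: shift | 0 SD | 0.10 SD | 0.17 SD | 0.34 SD |
| 6 of 30: false-positive rate | 5% | 6.8% | 9.8% | 28% |

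The simulated 0.34 SD is the finite-sample counterpart of the 0.35 SD from the formula.

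On a responder scale, with 55% in both arms and a response rate r among those removed, the bias is (0.55 − d·r)/(1 − d) − 0.55. For d = 0.20 this is 0 at r = 0.55, +7.5 points at r = 0.25 and about +14 points at r = 0.

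**5. Does the text make removal decide the analysis?** The Drop-out criteria do not say that dropped children leave the analysis. Quality control attaches a label to non-compliance and no consequence. Data management and monitoring still seeks data from those who stop or deviate. Two things keep the question open: the sample size is inflated for dropout, which suggests some loss of outcomes, and YGTSS calls for observation in clinic, which a telephone call may not replace.

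**The case against.** A reader might infer that these rules do bias the YGTSS comparison, and in favour of acupuncture. The documents do not support that, for four reasons.

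- No section takes dropped or non-compliant children out of the analysis, and the article plans to keep collecting their data. The analysis population is normally set in the SAP, which is not shown, so its absence here is no fault.
- Prior acupuncture is fixed before allocation and the item names no arm. Removal on it, applied equally and blind, costs numbers but does not distort the contrast.
- The severe-reaction item names no arm either. The Adverse events section expects allergy, pain and distress under sham, so it cannot be said that only the real-needle arm loses children. No rates are given, and nothing links such reactions to worse tics.
- The 0.35 SD figure needs exactly the worst fifth of one arm to leave and nobody to leave the other.

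All four stand, and they limit the point to a conditional one. It might also be said that the experimental group in Quality control is loose wording for trial participants, since that section calls the trial protocol the experimental protocol. But under Randomization and in the intervention sections the term means the real-acupuncture arm, so the sentence as written covers one arm.

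The objection does not reach the two drafting faults. The eligibility and drop-out sections disagree about the same child, and sham attendance that was never counted cannot be recovered by any later analysis plan.

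**Conclusion.** Two stated rules are badly fixed. A screening fact sits among the drop-out criteria, which can waste randomised places in a 60-child sample and leaves room for selective removal by someone who knows the allocation. Compliance is defined for one arm only, which rules out a symmetric compliance or per-protocol comparison from the counts the protocol provides for.

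Bias in the YGTSS contrast is possible but not established. It arises only if these rules, or drop-out for severe reactions, govern who is analysed or who has a week-12 score. Its size would run from zero, when removal is unrelated to outcome, to about 0.35 SD when the worst 20% leave one arm only. The removal shares and correlations behind that range are assumptions, not figures from the documents. This should be fixed, but it does not by itself invalidate the trial.

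**What to change.** - **Reconcile eligibility with drop-out.** Make prior acupuncture an eligibility item, checked at Week -1 before allocation, and take it out of the drop-out criteria.
- **Count sessions in both arms,** against the same 36 and with the same limits.
- **State what the criteria do not do.** Meeting a drop-out or compliance criterion does not by itself remove a randomised child from the YGTSS comparison.
- **Seek the week-12 in-clinic YGTSS** for every child who stops treatment, with telephone contact as the fallback.

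The cost is a short amendment. A few children are screened out earlier, and sham sessions, which are already scheduled, are also logged. The Trial status section says recruitment is still under way, so the screening check and the sham counts can still be put in place prospectively; uncounted sham sessions may not be recoverable once the trial is complete.
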